# Muscular Assessment in Patients With Severe Obstructive Sleep Apnea Syndrome: Protocol for a Case-Control Study

**DOI:** 10.2196/30500

**Published:** 2021-08-06

**Keywords:** myofunctional therapy, sleep apnea, sleep disordered breathing, speech therapy, phenotype, sleep, therapy, protocol, muscle, assessment, case study, exercise, airway, respiratory

## Abstract

**Background:**

Myofunctional therapy is currently a reasonable therapeutic option to treat obstructive sleep apnea-hypopnea syndrome (OSAHS). This therapy is based on performing regular exercises of the upper airway muscles to increase their tone and prevent their collapse. Over the past decade, there has been an increasing number of publications in this area; however, to our knowledge, there are no studies focused on patients who can most benefit from this therapy.

**Objective:**

This protocol describes a case-control clinical trial aimed at determining the muscular features of patients recently diagnosed with severe OSAHS compared with those of healthy controls.

**Methods:**

Patients meeting set criteria will be sequentially enrolled up to a sample size of 40. Twenty patients who meet the inclusion criteria for controls will also be evaluated. Patients will be examined by a qualified phonoaudiologist who will take biometric measurements and administer the Expanded Protocol of Orofacial Myofunctional Evaluation with Scores (OMES), Friedman Staging System, Epworth Sleepiness Scale, and Pittsburgh Sleep Quality Index questionnaires. Measures of upper airway muscle tone will also be performed using the Iowa Oral Performance Instrument and tongue digital spoon devices. Evaluation will be recorded and reevaluated by a second specialist to determine concordance between observers.

**Results:**

A total of 60 patients will be enrolled. Both the group with severe OSAHS (40 patients) and the control group (20 subjects) will be assessed for differences between upper airway muscle tone and OMES questionnaire responses.

**Conclusions:**

This study will help to determine muscle patterns in patients with severe OSAHS and can be used to fill the gap currently present in the assessment of patients suitable to be treated with myofunctional therapy.

**Trial Registration:**

ISRCTN Registry ISRCTN12596010; https://www.isrctn.com/ISRCTN12596010

**International Registered Report Identifier (IRRID):**

PRR1-10.2196/30500

## Introduction

### Background

Obstructive sleep apnea-hypopnea syndrome (OSAHS) is a significant public health issue characterized by repetitive episodes of airway obstruction during sleep associated with snoring, sleep fragmentation, daytime sleepiness, and increased cardiovascular risk [1,2]. It is well established that the most effective treatment for OSAHS is continuous positive airway pressure (CPAP) [3], which has variable patient compliance. CPAP virtually eliminates OSAHS and snoring, reduces daytime sleepiness, and improves subjective sleep quality [3,4].

The etiology of OSAHS is multifactorial, including anatomical and physiological factors. The upper airway dilator muscles are crucial for maintaining pharyngeal patency and may contribute to the incidence of this medical condition [5,6].

Other treatments for OSAHS include a mandibular advancement device (MAD), conventional surgery, CO_2_ or radiofrequency laser, or hypoglossal nerve stimulation. There is also some evidence for pharmacological treatments with oxybutynin and atomoxetine, which are currently showing promising results [7]. Clinical trials have been carried out with theophylline, acetazolamide, and desipramine to reduce the collapse of the upper airway, but without clear effectiveness [8,9].

Myofunctional therapy is a treatment applied to patients with orofacial myofunctional disorders that can interfere with the development or functioning of orofacial structures and functions [10]. Reviews of studies on myofunctional therapy show benefits by promoting changes in dysfunctional muscles of the upper airway [11]; therefore, this treatment has been proposed to reduce the severity of OSAHS and associated symptoms in adults [12]. Myofunctional therapy also has potential to promote a decrease in the Apnea-Hypopnea Index (AHI), reduce snoring [13], and improve quality of life [14]. In addition, it can be considered as an adjuvant therapy and an intervention strategy to support CPAP adherence [15].

However, it is currently unknown which patients are the best candidates for myofunctional therapy. Although there are instruments available for patient selection such as the Expanded Protocol of Orofacial Myofunctional Evaluation with Scores (OMES), involving functional exploration of all of the stomatognathic functions to obtain a score, this has proven to be inferior in patients with OSAHS compared with controls [16,17]. A myofunctional therapist uses this evaluation to improve the examined items that are in deficit and subsequently performs specific exercises to improve them. However, the OMES test is based on subjective evaluations, contains many items, and is difficult to reproduce. In our opinion, a more concise, objective, and reproducible evaluation is required. This opinion stems from our experience of measurements with the Iowa Oral Performance Instrument (IOPI) of the genioglossus muscle and the orbicular muscle [18,19]. Together with measurement of the motor tone of the genioglossus muscle using a tongue digital spoon (TDS) [20], these simple measurements may provide patients with information about their condition, serve as therapy response parameters, and objectively transmit results between professionals, which can also be based in electronic health facilities [21].

### Aim

The aim of this study is to evaluate the muscle patterns of patients with severe OSAHS. The use of the OMES protocol can be complemented by the values obtained through the IOPI and the TDS.

### Objectives

The main objective is to evaluate the function of the stomatognathic musculature of patients with OSAHS by using the OMES protocol, TDS, and IOPI.

The secondary objectives are to: (1) use this protocol to evaluate whether there are differences between the muscles of patients with OSAHS and healthy controls; (2) use the IOPI to measure tongue strength and resistance with the genioglossus and buccinator muscle tone, and evaluate whether there are differences from those of healthy patients; and (3) use the TDS to measure tongue pressure and evaluate whether there are differences from healthy patients.

## Methods

### Design

We designed a prospective controlled quasiexperimental pilot study on patients with severe OSAHS (Figure 1).

**Figure 1 figure1:**
[figure not shown]
Flow chart of the study process. IOPI: Iowa Oral Performance Instrument; OMES: Orofacial Myofunctional Evaluation with Scores; OSAHS: obstructive sleep apnea-hypopnea syndrome; TDS: tongue digital spoon.

### Scope of the Study

This study will involve patients diagnosed and/or treated at the Pneumology and Otorhinolaryngology Departments of Quirónsalud Hospital in Marbella (Malaga, Spain) or Hospital Campo de Gibraltar (Palmones, Cadiz, Spain) where the study will also be performed.

### Study Population

This study will include patients diagnosed with sleep apnea-hypopnea at the participating hospitals and who agree to participate in the project.

### Inclusion Criteria

For cases, adults (aged 18-75 years) who have received a diagnosis of severe OSAHS (AHI>30) without previous experience of the condition and not undergoing treatment owing to different circumstances, who had not undergone any previous treatment for OSAHS, and signed the informed consent form will be included.

For controls, adults with adequate sleep hygiene, no complaints of snoring or daytime sleepiness, and scoring <7 points on the Epworth Sleepiness Scale will be included.

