### Exclusion Criteria

Cases and controls alike with a cognitive or neurological deficit, inability to answer questionnaires, severe alcohol abuse, presence of craniofacial malformations, active neoplastic disease, or a history of prior orofacial muscle rehabilitation therapy and any prior apnea treatment that may modify the study results (surgery, MAD, CPAP) will be excluded.

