### Sample Size and Sampling Procedure

The effectiveness of use of the OMES protocol in the evaluation of patients with moderate to severe apnea-hypopnea syndrome will be evaluated from data previously published in studies using this protocol. Following the literature review, patients will be recruited. The sample size will be 60 subjects (40 in the experimental group and 20 in the control group). The sample size was calculated using the XLSTAT statistical software for Excel.

The variables that we are going to measure in all patients are reflected in the data collection table shown in Multimedia Appendix 1 using SPSS Info software, including age, sex, weight, height, ethnicity, BMI, abdominal circumference (at the level of the navel), neck circumference (using a flexible tape around the most prominent part while the patient is standing with their arms by their sides, head erect, and eyes looking ahead), IOPI measurement of tongue strength and the buccinator muscle, AHI, nighttime oxygen desaturation index, lowest overnight oxygen saturation levels, digital spoon measurement of tongue strength, and OMES protocol.

A series of questionnaires will be applied to both groups: Friedman Staging System, Epworth Sleepiness Scale, and Pittsburgh Sleep Quality Index (see Multimedia Appendix 2). An information sheet and information consent will also be provided and signed by patients.

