### Distribution of Hospital Visits

#### Selection Visit

A patient diagnosed with OSAHS at a pulmonology laboratory by means of an initial sleep study (with measurement of baseline AHI, nighttime oxygen desaturation index, and the lowest nighttime oxygen saturation figures) will be evaluated with respect to the inclusion and exclusion criteria and then informed about the study. After reading the information and having any doubts resolved, the patient will accept and sign the inform consent form in duplicate, taking one copy home.

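### Controls are called healthy without OSAHS being ruled out, and the article does not settle whether they have a sleep study; the case-control contrasts may be diluted

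*Protocol article*

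**What the plan says.** **Controls.** Under Inclusion Criteria they are "adults with adequate sleep hygiene, no complaints of snoring or daytime sleepiness, and scoring <7 points on the Epworth Sleepiness Scale". All of this comes from history or questionnaire; no sleep-study result is required.

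**Cases.** The same section takes adults "who have received a diagnosis of severe OSAHS (AHI>30"), with no symptom requirement.

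**Exclusions for both groups.** Under Exclusion Criteria, "any prior apnea treatment that may modify the study results (surgery, MAD, CPAP) will be excluded". Untreated or undiagnosed OSAHS is not on the list.

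**Measurement.** Sample Size and Sampling Procedure states: "The variables that we are going to measure in all patients are reflected in the data collection table". The list includes "AHI, nighttime oxygen desaturation index, lowest overnight oxygen saturation levels". The abstract applies the word patients to controls as well: "Twenty patients who meet the inclusion criteria for controls will also be evaluated".

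**Sleep study.** Selection Visit starts from "A patient diagnosed with OSAHS at a pulmonology laboratory by means of an initial sleep study". Experimental Design likewise ties the myofunctional evaluation to the week of polysomnography for patients diagnosed with OSAHS. No sleep study is described for controls.

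**Use of the group.** The first secondary objective is to "evaluate whether there are differences between the muscles of patients with OSAHS and healthy controls". The second and third make the same comparison for the IOPI and the TDS. The abstract's objective also names healthy controls.

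**The concern.** The case group is fixed by a sleep-study index. The control group is fixed by the absence of complaints, adequate sleep hygiene and a low Epworth score. None of the control criteria establishes that OSAHS is absent, so a person with undiagnosed OSAHS and no complaints can be enrolled and analysed as healthy.

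If such controls share some of the cases' muscular deficit, the control mean moves toward the case mean and the OMES, IOPI and TDS differences are underestimated. With only 20 controls, a few such people matter. A null or small difference could then mean either that the muscles do not differ or that the comparison group was mixed, and the reader could not tell which.

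The measurement text adds a second problem. Either controls have an AHI that eligibility does not use, or they have none and the variable list is wrong for them.

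**Working it through.** **1. The sections side by side**

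| Question | Where | Answer |
|---|---|---|
| AHI limit for cases? | Inclusion Criteria | Yes, above 30 |
| AHI limit for controls? | Inclusion and Exclusion Criteria | None |
| Undiagnosed OSAHS excluded? | Exclusion Criteria | No; prior treatment only |
| AHI listed for whom? | Sample Size and Sampling Procedure | All patients |
| Does patients cover controls? | Abstract, Methods | Used that way there |
| Sleep study described for whom? | Experimental Design; Selection Visit | Diagnosed patients only |

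The same variable list contains OMES, IOPI and the digital spoon, which controls must have if they are to be compared. That favours reading it as covering controls. The visit description points the other way.

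**2. Inputs for the size of the effect**

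- From the article: 40 cases, 20 controls, significance at P<.05.
- Not in the article: effect size, SD and power behind the total of 60, so that figure can be neither reproduced nor refuted.
- Assumed: two-sided test; a fraction f of controls with undiagnosed OSAHS; a share s of the cases' deficit carried by those controls.

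**3. Detectable difference**

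Standard error in SD units = √(1/20 + 1/40) = √0.075 = 0.274. With 58 degrees of freedom the critical value is 2.00. The difference with 80% power (non-central t) is 0.78 SD, used below as the assumed true difference d.

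**4. Dilution**

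Observed difference = d × (1 − f × s).

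| f | s = 1: difference | s = 1: power | s = 0.5: difference | s = 0.5: power |
|---|---|---|---|---|
| 0% | 0.78 | 80% | 0.78 | 80% |
| 10% | 0.70 | 71% | 0.74 | 76% |
| 20% | 0.62 | 61% | 0.70 | 71% |
| 30% | 0.55 | 50% | 0.66 | 66% |

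Example: f = 20%, s = 1 gives 0.78 × 0.80 = 0.62; 0.62/0.274 gives a non-centrality of 2.28 and power of 61%.

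The formula ignores the slightly larger spread of a mixed control group. A simulation of 40,000 runs at d = 0.8 that included it gave power about 1 point lower at most for f up to 30% (for example 62.1% against 63.2% at f = 20%, s = 1).

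**5. A larger true difference**

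With d = 1.0, power without contamination is 95%. At f = 10%, 20% and 30% it is 90%, 82% and 71% for s = 1, and 93%, 90% and 86% for s = 0.5.

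**6. Chance that at least one control is affected**

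1 − (1 − f)^20: for f = 10%, 1 − 0.9^20 = 88% (2 expected); for f = 20%, 1 − 0.8^20 = 99% (4 expected).

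**The case against.** The strongest reply is that the effect is modest and its direction is benign. The study is described as a pilot, its main objective is to evaluate muscle function in patients with OSAHS, and dilution works against finding a difference, so it would not manufacture one. Asymptomatic controls with milder OSAHS may carry little of the severe cases' deficit. The Discussion itself presents low muscle tone as one phenotype among others, so OSAHS in a control need not imply weak muscles. Figure 1, the database appendix and the full protocol are not shown and might settle whether controls have a sleep study. These points stand as limits on size and certainty. They do not supply a control criterion that rules out OSAHS, and the article states its eligibility criteria explicitly.

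Three stronger readings are tempting and should not be drawn:

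- *The two definitions admit the same undiagnosed person.* Cases must already have received a diagnosis, so someone undiagnosed fails the case rule whatever their AHI. Only a person already diagnosed, untreated and without complaints could meet both texts. The supported point is that undiagnosed OSAHS is not ruled out in controls.
- *Every analysis is diluted.* Only the case-control contrasts are. The description of cases, the rater reliability and the OMES-IOPI-TDS correlations are not weakened by this mechanism.
- *AHI is certainly available for all 60.* The list says all patients, but the next paragraph uses both groups for the questionnaires, which may signal a distinction, and no control sleep study is described. The article leaves this open.

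**Conclusion.** The point holds in limited form. As written, controls labelled healthy may have undiagnosed OSAHS, and the sections on eligibility, measured variables and visits do not agree on whether a sleep study would reveal it. The exposed analyses are the case-control differences in OMES, IOPI and TDS under the secondary objectives, with a tendency toward underestimation.

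The size is conditional. With a true difference of 0.78 SD and 10% to 30% of controls affected, power falls from 80% to between 71% and 50% if they carry the full deficit, and to between 76% and 66% if they carry half. With a true difference of 1.0 SD the loss is smaller. Contamination rate, share of deficit and effect size are all assumptions, and the direction requires that affected controls lie between unaffected controls and cases. The gap in the control definition depends on none of these.

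**What to change.** First state whether controls have a sleep study, and bring Sample Size and Sampling Procedure, Experimental Design and Selection Visit into line.

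**If they do:** exclude from the control group those who meet the laboratory's own diagnostic definition of OSAHS. At minimum, pre-specify a sensitivity analysis of the OMES, IOPI and TDS contrasts without them, and report the controls' AHI. The cost is one eligibility or analysis line and a few controls lost or replaced. Data had been collected for 20% of the planned sample (0.20 × 60 = 12 people), so this was still practicable when the article was written.

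**If they do not:** restrict AHI and the oximetry variables in the list to cases, and replace the healthy label in the objectives and conclusions with asymptomatic controls, OSAHS not excluded. State that differences may be underestimated. The cost is a wording change and a more cautious conclusion. Imposing an AHI limit in this situation would not be cheap: it would need about 20 additional sleep studies, plus those for any replacements.

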### Exclusion Criteria

Cases and controls alike with a cognitive or neurological deficit, inability to answer questionnaires, severe alcohol abuse, presence of craniofacial malformations, active neoplastic disease, or a history of prior orofacial muscle rehabilitation therapy and any prior apnea treatment that may modify the study results (surgery, MAD, CPAP) will be excluded.

### Sample Size and Sampling Procedure

The effectiveness of use of the OMES protocol in the evaluation of patients with moderate to severe apnea-hypopnea syndrome will be evaluated from data previously published in studies using this protocol. Following the literature review, patients will be recruited. The sample size will be 60 subjects (40 in the experimental group and 20 in the control group). The sample size was calculated using the XLSTAT statistical software for Excel.

The variables that we are going to measure in all patients are reflected in the data collection table shown in Multimedia Appendix 1 using SPSS Info software, including age, sex, weight, height, ethnicity, BMI, abdominal circumference (at the level of the navel), neck circumference (using a flexible tape around the most prominent part while the patient is standing with their arms by their sides, head erect, and eyes looking ahead), IOPI measurement of tongue strength and the buccinator muscle, AHI, nighttime oxygen desaturation index, lowest overnight oxygen saturation levels, digital spoon measurement of tongue strength, and OMES protocol.

A series of questionnaires will be applied to both groups: Friedman Staging System, Epworth Sleepiness Scale, and Pittsburgh Sleep Quality Index (see Multimedia Appendix 2). An information sheet and information consent will also be provided and signed by patients.

### Procedures

#### Experimental Design

A myofunctional evaluation of patients diagnosed with OSAHS will be performed in the same week as the polysomnography is performed. During this evaluation, patients will be blindly examined by a speech therapist and their examination will be recorded on video for subsequent evaluation.

The patient will sit 1 meter away from the camera with their feet flat on the floor and their back supported by the backrest. The camera (Sony CCD-TRV138 Handycam camcorder) will be placed on a tripod at face and shoulder height.

Evaluation with the OMES protocol (see Multimedia Appendix 3) will then take place, based on the analysis of the following parameters: (1) appearance/posture; (2) mobility; and (3) functions, including respiration, deglutition, and mastication.

As a result of this evaluation with the already validated protocol, the higher the score, the more normal the patient’s stomatognathic system.

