#### TDS Evaluation

Finally, the tone of the tongue muscles will be measured with a digital spoon, taking three measurements and using the highest obtained. A digital spoon is a kitchen tool used to estimate the weight of food. To develop the TDS, we used the Soehnle Cooking Star Digital Measuring Spoon with graduation from 0.1 grams to 500 grams (ID ID20005876833). This is a handheld instrument with a spoon that can be found on online shopping platforms, consisting of a handle where the “tare” and “hold” buttons are located. Pressing the “hold” button helps to obtain the highest tared value, equivalent to the IOPI peak pressure. To carry out the measurements, the spoon is inverted and a 1-cm^2^ circular sticker is placed on the back to obtain a marked circumference. To measure tongue strength, the subject holds the spoon by the handle and, with their elbow resting on a flat surface, brings the spoon closer to the tongue with an elbow angle of approximately 30°. The subject must then tare the device by pressing the “hold” key, marking 0.0 grams. The subject then presses on the marked circumference with the tip of their tongue. Once done, with the index finger of the hand that is holding the handle, the subject presses the “hold” button. This test is performed entirely by the subject to avoid movements on the spoon that may interfere with the results [20].

The recordings and the data obtained will also be analyzed by another blinded examiner.

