#### One-off Visit

The patient will be evaluated by the speech therapist and fill in the sleepiness questionnaires, following which the OMES protocol will be applied and the evaluation will be carried out with the IOPI and the TDS.

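### The examiner described as blind is also assigned the sleepiness questionnaires, which come before the subjective OMES rating and partly define the control group

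*Protocol article*

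**What the plan says.** All references are to the protocol article.

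- **Blinding claim (Experimental Design).** "patients will be blindly examined by a speech therapist and their examination will be recorded on video for subsequent evaluation". The text does not say whether the therapist is blind to group, to the AHI or to both.
- **Tasks of the examiner (abstract, Methods).** "Patients will be examined by a qualified phonoaudiologist who will take biometric measurements and administer the Expanded Protocol of Orofacial Myofunctional Evaluation with Scores". The same sentence adds the Friedman, Epworth and Pittsburgh instruments.
- **Order at the visit (One-off Visit).** The section reads: "The patient will be evaluated by the speech therapist and fill in the sleepiness questionnaires, following which the OMES protocol will be applied". The IOPI and TDS measurements come after that.
- **Control definition (Inclusion Criteria).** Controls need an Epworth score below 7, no snoring or sleepiness complaints, and adequate sleep hygiene. No Epworth limit is set for cases.
- **Nature of OMES (Background).** The authors describe it as resting on subjective judgement and hard to reproduce.
- **Second examiner (TDS Evaluation).** "The recordings and the data obtained will also be analyzed by another blinded examiner". The abstract gives this second reading one purpose, agreement between observers.

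**The concern.** A blind rating protects the case-control comparison only if the rater has no information about group when the score is given. Here the stated roles and the stated order put a group-defining questionnaire in the hands of the rater, or at least within reach, before OMES is scored. OMES is named first in the main objective. The direction expected is also on record: the Background section reports lower OMES scores in patients with OSAHS than in controls. A rater who knows or suspects the group could, without intending to, score towards that expectation. Part of an observed OMES difference could then come from the rating and not from the musculature, and no later analysis of the live scores could separate the two.

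**Working it through.** The plan gives no figure on this point to reproduce. The check has a textual part and two illustrations.

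**1. The sections side by side**

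| Question | Answer in the article | Where |
|---|---|---|
| Is the live examiner blind? | Yes; to what is not said | Experimental Design |
| Who handles Epworth and Pittsburgh? | The phonoaudiologist who also does OMES (administers) | Abstract, Methods |
| Who completes them? | The patient (fills in) | One-off Visit |
| Before or after OMES? | Before | One-off Visit |
| Does Epworth bear on group? | Yes, controls score below 7 | Inclusion Criteria |
| When are neck and abdomen measured? | Not stated | Listed only, in Sample Size and Sampling Procedure |

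The article uses the terms phonoaudiologist and speech therapist for what reads as one role. On that reading, the blinding claim conflicts with the roles and order unless the examiner is kept from the answers, and no sentence says so.

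**2. How much Epworth alone gives away**

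Inputs: 40 cases and 20 controls (Sample Size and Sampling Procedure), with every control below 7. Let f be the share of cases scoring 7 or more. The documents do not give f, so it is varied.

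- Cases identified with certainty = 40f.
- P(case | score below 7) = 40(1 − f) / [40(1 − f) + 20].
- Best-guess accuracy = [40f + max(40(1 − f), 20)] / 60.

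| f (assumed) | Cases identified | P(case, score below 7) | Best-guess accuracy |
|---|---|---|---|
| 0.5 | 20 | 20/40 = 0.50 | 40/60 = 67% |
| 0.7 | 28 | 12/32 = 0.38 | 48/60 = 80% |
| 0.9 | 36 | 4/24 = 0.17 | 56/60 = 93% |

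Always guessing case is right for 40/60 = 67%. At f = 0.5 overall accuracy is therefore no better than that, although 20 cases are known for certain.

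**3. What a rating shift would do to the test**

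Assume no true difference and a rater-induced shift of b SD in the difference between group means. Take a t test at 0.05, two-sided (the article gives P<.05 without sidedness), with 40 + 20 − 2 = 58 degrees of freedom and critical value 2.002.

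- Noncentrality = b / √(1/40 + 1/20) = b / 0.2739.
- False-positive rate = P(|T| > 2.002) under the noncentral t distribution.

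| b (assumed) | Noncentrality | False-positive rate |
|---|---|---|
| 0 | 0 | 5.0% |
| 0.10 | 0.365 | 6.5% |
| 0.125 | 0.456 | 7.3% |
| 0.25 | 0.913 | 14.6% |
| 0.40 | 1.461 | 30.1% |
| 0.50 | 1.826 | 43.5% |

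The lower rows matter. If half of the cases are identified and only those are scored lower, by 0.25 to 0.50 SD each, the group shift is 0.5 × 0.25 = 0.125 to 0.5 × 0.50 = 0.25 SD, and the rate is 7.3% to 14.6%.

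**The case against.** The other side has several good arguments.

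- **The examiner may never see the answers.** The visit description has patients fill in the questionnaires, and administering a form does not require reading it before OMES. This stands as a possibility. It also means that two sections describe the task differently and that nothing states the answers are withheld.
- **Epworth does not reveal everyone's group.** Correct. Only a score of 7 or more is decisive, because a lower score fits either group.
- **The second examiner is blinded.** This is a real safeguard. A reader might infer from "The recordings and the data obtained will also be analyzed by another blinded examiner" that this person receives the questionnaires or the first rater's scores. The text does not say that. The sentence closes the TDS section, and the data may be only the instrument readings. What remains is that the term is undefined and that the reading is assigned to concordance, not to the group comparison.
- **Body measurements.** A reader might infer that neck and abdominal circumference are taken before OMES because the abstract lists biometrics first. No section states that order, and body size is in any case visible to a live examiner.
- **IOPI and TDS.** A reader might extend the concern to these. They are instrument readings, the IOPI encouragement is given to every participant, and the TDS test is carried out by the subject. They are less exposed, and differential encouragement would be speculation.
- **The bias size is assumed.** Correct. Nothing in the documents supports a particular value.

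**Conclusion.** The point holds in a limited form. The article claims a blind live examination, yet its own roles and visit order allow the OMES rater to be unmasked by a questionnaire that helps to define the controls. Unmasking would be certain for participants scoring 7 or more on Epworth and probabilistic for the others, and it depends on the examiner seeing the answers, which the text neither states nor prevents. The exposure is mainly to OMES.

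It would go too far to conclude that group membership is known for everyone, or that the second reading is itself unblinded. The false-positive range of 6.5% to 43.5% rests on assumed shifts of 0.10 to 0.50 SD, no true difference and a two-sided t test. It illustrates sensitivity to rater bias and does not estimate it. This is a cheap improvement worth making, not a flaw that invalidates the study.

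**What to change.** 1. **Visit order (One-off Visit).** Carry out OMES, then IOPI and TDS, before the questionnaires and body measurements. Alternatively, have the questionnaires self-completed and kept from the examiner until the OMES score is locked. Align the abstract with whichever is chosen.
2. **Blinding statement (Experimental Design).** Say what the examiner is blind to: group, sleep-study results and questionnaire answers.
3. **Second examiner (TDS Evaluation).** Supply only coded videos, with cases and controls in mixed order, and without first-rater scores, questionnaires or sleep data. This also keeps the concordance estimate independent.
4. **Sensitivity analysis (Statistical Analysis).** State in advance that the case-control OMES comparison will be repeated with the blinded video score, including re-scored videos of participants already examined. Making the video score the main outcome is more debatable, because video may miss live cues.

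**Cost.** The changes concern visit order and file handling. The camera and second examiner are already planned, so no staff are added. The Results section reports data collected for 20% of the planned sample, that is 0.20 × 60 = 12 participants, who were presumably seen under the existing order. The report should say so. Their recordings allow the blinded re-scoring in item 4.
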